### Clinical evaluations

The main morbidity outcome will be incidence of clinical disease assessed by PCD; data from this will provide the primary endpoint of the study. PCD is considered to generate information of more direct relevance to public health than active case detection and is thus more suitable for evaluating population level malaria interventions [16]. Mild malaria and parasitaemia is common in all children in this area of highly seasonal malaria [17,18] and we will enrol children aged 6 months - 13 years. We previously developed a system in Gambian villages where a trained MRC nurse provided diagnostic support to the established VHW in the study villages [19]. Following this experience, in this study the nurses will provide training and ongoing support to the VHW for diagnosis of malaria in consulting study children who report with a history of fever in the last two days using RDT and treatment of malaria. Study nurses at the health facilities will document episodes of malaria in study children who present directly to them on the Case Report Form (CRF). At the health facilities malaria diagnosis will also rely on the use of RDT but, in addition, thick blood films will be made for later staining with Giemsa and microscopy to estimate parasite density in this subset of cases. To facilitate documentation of all clinical events (i.e. clinical consultations by study children), all enrolled children will be issued with enumerated photo identity cards; the study number and village will be recorded for all clinical events on the CRF. The project field workers or nurses that visit each VHW will complete the CRF for all study subjects that consult with the VHW.

All children present in their villages at the surveys will be clinically examined for obvious symptoms and signs of illness, temperature and spleen enlargement. A sample of all the study children, at least 50/village cluster will be randomly selected stratified by age, and these as well as those reporting fever in the last 48 hours and/or with a temperature of ≥37.5°C will be finger pricked for immediate measurement of anaemia and presence of parasites by RDT. Anaemia will be assessed by measuring haemoglobin concentration using a spectrophotometer (HaemoCue^®^) in the field.

The primary endpoint selected is the definition of malaria used in The Gambia in research studies and in the National Treatment Guidelines [18,20,21]. However, a parasite cut-off level may increase specificity but the gain in specificity cannot be known in advance with the changing infection rates [12,13]. We thus also intend to use the logistic regression method of Smith and colleagues [22] to examine the effect of parasite cut-off on the specificity and sensitivity on the definition of clinical malaria. This method has recently been endorsed by a WHO study group for use in studies defining malaria vaccine efficacy [14].

### Entomological evaluations

Exposure to mosquitoes will be measured by surveillance with light traps and house exit rates estimated using window traps to obtain the primary entomological endpoint [23]. A CDC miniature light trap will be positioned close to one sleeper protected with a LLIN. Two estimates of EIR and the number of sporozoite infective bites/child/season will be calculated: 1 based on light traps collections and 1 from window traps. Parity will be recorded separately from both trap types.

### Study procedures and evaluations

In advance of the spray campaign in year 1, spray operatives and supervisors will be trained on the WHO methods for IRS with DDT for two weeks by the NMCP vector control officer seconded to the project and an internationally recognized IRS consultant. They will be equipped with personnel protective clothing, including boots, long-sleeved cotton overalls, hat, gloves, mask and boots and trained in the maintenance and use of these. Spray operatives will use spray pressurized canisters made to WHO specifications WHO/VBC/89.970 (Hudson X-Pert^® ^Sprayer, 15L model 67422AD with stainless steel nozzle (8002E), flat fan pattern, 80° angle, flow rate 0.76L/min at 45psi pressure). They will be rigorously trained in the use of these and their maintenance. A 2-day refresher training will be provided before the spray campaign in year 2. Any remnant in the sprayers at the end of daily spraying will be collected following the "Progressive Rinse" method and recycled to minimize waste (http://www.hdhudson.com/global-public-health/newsletters/technical-information accessed 9th June 2011).

It is intended that both IRS and LLIN distribution will be completed in May both years. In year 2 all households in the arm randomized to this intervention will receive IRS as in year 1. LLIN distribution in year 2 will be to residents who have relocated to study villages since year 1.

Village health workers will be provided with refresher training on diagnosis of malaria, the use of RDT and study procedures in July 2010 by the study physician in collaboration with study nurses and the community health nurses. The methods used will be informed by ongoing studies in The Gambia on the introduction of RDT at all levels of health service. Refresher training will be provided in 2011 before the transmission season.

Movement of children will be assessed at monthly intervals on brief questionnaires to estimate the time at risk and bednet usage will be assessed during these house visits in August each year.

Thick blood films will be stained with Giemsa and examined under 1000-fold magnification by trained, experienced microscopists. Parasite counts will be recorded per high power field and 100 fields will be counted before a slide is declared negative. Parasite density will be estimated assuming that one parasite per high power field equals 500 parasites/μl [24]. Two slides will be prepared from each subject and read separately by two experienced microscopists; discrepancies will be resolved by a third reader.

Mosquitoes will be identified by microscopy and the numbers of *An gambiae *s.l. and other species recorded. The presence of sporozoites in *An gambiae s.l. *will be identified using an enzyme-linked immunosorbent assay [25] and *An. gambiae s.l. *females will be typed to the species by PCR [26].

### Safety considerations

There are no apparent risks to the safety of individuals or communities in this study. Permethrin-treated long lasting nets and DDT IRS has been fully evaluated by the WHO Pesticide Evaluation Scheme and approved for vector control (http://www.who.int/whopes/en/), and the products will be used in compliance with their recommended use and guidelines.

All children enrolled in the trial will have access to malaria diagnosis and treatment according to Gambian National Treatment Guidelines and all visits to the VHW or health facilities will be documented on the CRF.

In the case that a participant develops a serious adverse event (SAE) during the course of the study this will be captured on the CRF for PCD if it is associated with a confirmed or suspected malaria episode. When a study child consults with the VHW with a severe illness that is not malaria, this will be captured in the VHW daily log. The CRF for PCD or the details from the VHW daily log will be submitted to the study physician by the nurse or fieldworker responsible for the village-cluster on a weekly basis. If it is a serious adverse event (SAE) the study physician will record and manage the SAE in accordance with Good Clinical Practice (GCP).

The study physician will check all CRF regularly, at least once a week, and will inform the IDMC of the numbers of malaria attacks and SAE by village as required by the ID. Suspicion of potential harm to participants or the environment caused by the interventions may lead to discontinuation of the study. Excessive clustering of SAE by village(s) will be reported to the study's Data Monitoring and Ethics Committee.

If an individual wants to terminate his/her participation, no further follow-up will be performed. In the case of a study child leaving during year 1, they will be replaced in year 2 of the study (June 2011). There will be no replacement during the surveillance period either year. If a household withdraws consent, no further follow-up will be made and there will be no replacement. If a village opts out of the study before July in either year replacement by a neighbouring village will be considered.

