## Methods/Design

### Study area and participant eligibility

The study is situated in the far east of The Gambia, in URR, extending approximately 240 to 320 km inland from the mouth of the Gambia River on the Atlantic coast, an area of open Sudan savanna. The climate consists of a single rainy season from May to October followed by a long dry season. This defines the highly seasonal malaria transmission with most malaria episodes experienced during or immediately following the rainy season. This region covers an area of 1995 km^2 ^and is bisected by the river into the north and south banks. The population of the region was 182,586 in 2003, the most recent census, with the majority living in small rural villages in houses made with mud or cement walls and thatched or metal roofs. The study's field station is based at Basse Santa Su town (UTM coordinates 13.3167N, -14.2167W) which is the only sizeable urban area.

Villages or groups of neighbouring villages, will be selected for the study that have > 110 children aged 6 months -13 years and that are ≥2 km from another study village to reduce likelihood of movement of mosquitoes from one cluster to the next. The study cohort of children, aged 6 months - 13 years old in June in Year 1, who are village residents, will be enumerated and an average of 110/cluster will be selected randomly and invited to participate in the clinical surveys and passive case detection (PCD). In order for the results from this study to be as generalizable as possible, no distinctions will be made regarding gender, ethnic group, medical condition or physical health. Children will be included providing their carers/parents give witnessed informed written consent and, in the case of older children, assent is provided. Assurance will also be sought from carers/parents that they expect that the child will remain resident in their village during the transmission season and will not be sent away for example for live stock herding or schooling. Subjects and households are free to withdraw from participating in the study at any time without giving a reason. If consent is not provided then replacement children will be randomly selected from those remaining. In year 2, overage children will leave the study and infants aged 6 to 18 months will be recruited; any other children who have left the study, for whatever reason, will be replaced.

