### Design

A cluster-randomized controlled study design will be used, as IRS is a community-level intervention and the village cluster as a suitable unit for randomization. All households in all the clusters will be offered LLIN at no cost to the recipients to enable all residents to benefit from this intervention. The clusters will then be randomized into two equal groups; all households in the villages in one group will be offered IRS and those in the other group will not. It is not possible to conduct the IRS in a blinded manner since a placebo would quickly be identified by the community as non-protective. To assess whether DDT IRS and LLINs combined provide better protection against clinical malaria in children than LLINs alone, 75- 125 children aged from 6 months to 13 years old will be sampled according to cluster size enrolled into a study cohort. These children will be followed during the malaria transmission season in 2010 and 2011. Clinical malaria will be recorded by study staff using PCD in close collaboration with government health workers both at the village and health facility levels. Parasites will be detected by a rapid diagnostic test (RDT, Paracheck Pf, Orchid Biomedical Systems, Goa, India) and treatment will follow government treatment guidelines.

The study cohort will be surveyed for malaria indices (parasite prevalence, anaemia and spleen rate) at the end of both transmission seasons to generate data for the secondary endpoints and also at baseline before the year 1 transmission season. Baseline data will be used to compare the 2 groups before the interventions and end of season survey data will be used to attempt to define a *Plasmodium falciparum *parasitaemia cut-off giving optimum sensitivity and specificity for malaria cases in this setting [14].

Exposure to malaria vector mosquitoes and parasites indoors will be assessed using CDC light traps and window traps every 4 weeks from June to December and every 8 weeks from January to May in at least 6 randomly selected households in 16 village clusters in each arm of the study. This will be followed by detection of *Anopheles gambiae *species, parity status and sporozoite infection. A schematic representation of the trial is shown in Figure 1.

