### Interventions

#### a) Indoor-residual spraying

In study clusters randomized to IRS, indoor residual spraying will use a wettable powder of DDT (DDT- WP 75) manufactured to WHO specifications and supplied by Hindustan Insecticide Ltd., New Delhi, India. Indoor surfaces will receive DDT (2 g/m^2^), in May/June, at the start of the main malaria transmission season, in 2010 and 2011. DDT-WP 75, contains 500g of DDT per 670g of product and is packaged in 670g/sachets for making up to 10L with water. The sachets are clearly labelled following WHOPES guidelines (WHO/CDS/WHOPES/2003.7) and are delivered 25/heavy duty carton.

DDT will be stored to maintain efficacy and avoid environmental contamination according to WHOPES guidelines (WHO/CDS/WHOPES/2003.7) and in accordance with the Gambian National Environmental Agency's regulations. Thus the study DDT will be stored in a similar manner to DDT being used currently by the NMCP. The cartons containing individual sachets will be clearly marked with the study name (SANTE) and stored in a locked designated area in the Central Medical Stores until the week before the IRS campaign, each year, when they will be moved to a locked designated area at the Regional Store in Basse. While in the Central and Regional Stores the DDT will be under the control of the NMCP Study Investigators, who will supervise the interventions. The product will be supplied with an expiry date 2-years post-manufacture which will extend beyond June 2011.

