During the week before spraying, the sensitization team will inform villages that their village has been selected for IRS, the purpose of spraying, what is required of householders and the excepted IRS date. On the day of IRS, trained spray personnel will inform householders of the spraying schedule and repeat the purpose of spraying and what is required of householders. They will then allow the household time to prepare and vacate the house. Occupants must leave houses before spraying and any rooms occupied by sick people who cannot be moved will not be sprayed. The householder should remove all household items, including water, food, cooking utensils and toys from the house. When possible furniture should be moved outside; if this is not possible, it should be moved to the middle of the room to allow easy access for spraying walls and covered. All wall hangings should be removed. When water-jars cannot be removed they should be covered. Pets and domestic animals should be tethered away from the house. Rooms will not be sprayed if people or animals are present, if household items are not correctly removed or positioned or if the walls are covered with gloss paint. Thatch ceilings also will be sprayed but not tin or hardboard ones. Data will be collected on interior wall surfaces at baseline. Householders will be allowed back into their houses after spraying and will be asked to mop any excess solution from the floors and wash the floors with water before they allow children back into the house. They are requested not to wash, paint or re-plaster sprayed walls at least until the end of the malaria transmission season.

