### Sample Size Rationale

#### a) Clinical

Both LLINs and IRS alone reduce malaria morbidity by approximately 50% [5,6]. The combined impact of these two interventions is unknown. If the effects were simply additive a mean reduction of 75% could be anticipated for the combination, but the effects may be synergistic (e.g. by having a mass killing effect) or antagonistic (e.g. the repellency of DDT reducing *Anopheline *house entry and contact with LLINs). To cover these possibilities we expect that LLINs will reduce incidence by 50%, with LLINs and IRS combined reducing the residual incidence by 30-60% (i.e. 50% vs 65-80% fewer clinical cases of malaria). A study of 3-60 month old children during the end of the rainy season (Sept-Dec) in the URR in 2007 found a seasonal incidence of 0.79 (95% CI: 0.58-1.08) cases/child-years by PCD ([name] pers. comm.); ITN prevalence was 50%. We estimate conservatively that increasing LLIN provision to > 80% and inclusion of older children will reduce incidence rates by about 60-80%, so incidence rates of 0.30 (LLINs) to 0.15 cases/child-years (LLINs & IRS) have been included in the sample size estimations. The study will also record PCD over two high transmission seasons, not 1 as in the [name] study, further enhancing our ability to detect differences between study arms. Estimations for k, the corrected coefficient of variation to adjust for between cluster variation (based on within and between cluster variation) [27], from a cluster trial conducted in the Central River Region of The Gambia in 2006/7 ([name] personal communication) varied from 0.31-0.43 and has been used to explore sample sizes (Figure 2). Two of the 5 districts in URR have 70 villages suitable for the trial with over 100 children aged 6 months-14 years (predicted from the 2003 National Census) and could accommodate an average cluster size of 110 children (range 75-125). We plan to follow these children for 22 weeks covering the peak malaria incidence season each year, which, allowing for a 20% drop out rate over the 2 years, yields 74.4 child-years per cluster. The graphs below indicate a sample size of 5-39 clusters per arm (Figure 2). Since estimates for incidence and drop-out rate are conservative and the value of k may also be reduced by the stratified design, we will recruit 35 clusters in each arm of the trial.

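### The rule letting a neighbouring village replace one that opts out before July still applies after allocation is known, so non-randomised villages can enter the primary comparison

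*Protocol article*

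**What the plan says.** Under Safety considerations the protocol article gives the rule: "If a village opts out of the study before July in either year replacement by a neighbouring village will be considered". It does not say which arm the replacement joins, how it is picked among neighbours, whether it is randomised, or how the village that left is treated.

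Other sections fix the timing and the structure:

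- **Allocation.** Design: "The clusters will then be randomized into two equal groups; all households in the villages in one group will be offered IRS". The same section says "It is not possible to conduct the IRS in a blinded manner".
- **Disclosure.** Interventions, Indoor-residual spraying: "During the week before spraying, the sensitization team will inform villages that their village has been selected for IRS". Spraying takes place "in May/June, at the start of the main malaria transmission season, in 2010 and 2011".
- **Year 2.** Study procedures and evaluations has the same arm sprayed again in 2011. It limits year 2 net distribution to people who have moved into study villages since year 1.
- **Separation.** Study area and participant eligibility requires at least 2 km "from another study village to reduce likelihood of movement of mosquitoes from one cluster to the next".
- **Analysis.** Analytical plan, Outcome 1 takes the ratio of un-weighted mean cluster rates as the initial estimate of effect.

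**The concern.** The village cluster is the unit of randomisation, and 35 per arm is a small number on which to rest comparability. A neighbour brought in after allocation was never randomised to its arm. It is there because another village left, and someone who knew the allocation chose to fill the gap with this one. Because replacement is only to be considered, the decision is made case by case by unblinded staff.

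In an open trial, the decision to leave can depend on the arm. Only IRS villages are asked to accept spraying, and by 2011 all villages have had a season's experience of their allocation. Opt-out, and with it replacement, could therefore differ between arms. What is at stake is whether the primary comparison remains one between groups formed by randomisation.

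**Working it through.** **Step 1: where the window falls.** In year 1, IRS villages are told in the week before spraying, and spraying is in May/June. An opt-out between that notice and the end of June is within the rule and follows disclosure. The randomisation date is not given, so an earlier year 1 opt-out may precede randomisation, and replacing that village would do no harm. In year 2 the arms carry over, so every opt-out before July 2011 follows allocation.

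**Step 2: leverage of one replacement.** With un-weighted means, each full cluster carries 1/35 of its arm's mean. Suppose m clusters leave an arm and are replaced by clusters whose rate is r times the mean of those remaining. The arm mean, relative to not replacing, becomes

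((35 − m) + m·r)/35 = 1 + (m/35)(r − 1).

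Both m and r are assumptions; the documents give neither. If the IRS arm is affected and the rate ratio from the remaining clusters is 0.70:

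| m | r = 0.5 | r = 1 | r = 2 |
|---|---|---|---|
| 1 | 0.69 | 0.70 | 0.72 |
| 2 | 0.68 | 0.70 | 0.74 |
| 5 | 0.65 | 0.70 | 0.80 |

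The shift goes either way and is nil at r = 1. The table shows leverage and does not estimate bias.

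**Step 3: reproduce the planned sample size.** Inputs from Sample Size Rationale, Clinical: rates 0.30 and 0.15 per child-year, reductions of 30–60%, k from 0.31 to 0.43, and 74.4 child-years per cluster (110 × 22/52 × 2 × 0.8 = 74.46). Two-sided 5% and 80% power are assumptions, since the section states neither for this endpoint. With v = λ/y + k²λ² in each arm,

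c = 1 + (1.960 + 0.842)² × (v₀ + v₁)/(λ₀ − λ₁)².

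- λ₀ = 0.30, λ₁ = 0.12, k = 0.31: 1 + 7.849 × (0.012681 + 0.002997)/0.18² = 4.80, so 5.
- λ₀ = 0.15, λ₁ = 0.105, k = 0.43: 1 + 7.849 × (0.006176 + 0.003450)/0.045² = 38.31, so 39.

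This matches the stated range of 5–39 clusters per arm.

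**Step 4: power if lost clusters are not replaced.** With the same variances,

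power = Φ[(λ₀ − λ₁)/√(v₀/(n₀ − 1) + v₁/(n₁ − 1)) − 1.960],

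at a 30% reduction and k = 0.43, where λ₀ is the rate in the LLIN-only arm:

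| Clusters, LLIN-only vs IRS | λ₀ = 0.30 | λ₀ = 0.15 |
|---|---|---|
| 35 vs 35 | 83.9% | 76.3% |
| 35 vs 33 | 83.1% | 75.3% |
| 33 vs 33 | 81.6% | 73.7% |
| 35 vs 30 | 81.7% | 73.7% |

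These rows treat a lost cluster as contributing nothing. A village that leaves in year 2 keeps its year 1 person-time, so its cost would be smaller.

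**The case against.** The strongest reply is that this is a contingent, discretionary provision for a village leaving the study. The protocol does not say that the departed village's data are dropped or that a replacement enters the primary comparison. Analysis sets are commonly left to a statistical analysis plan, which is not shown. Some year 1 opt-outs may come before randomisation. A cluster may be a group of villages, so one replacement may change only part of a cluster. All of this is fair and lowers the severity. It does not remove the point, because the rule is written with a window that runs past allocation in both years.

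Several stronger readings are tempting but not supported:

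- **That the rule selectively alters the IRS arm.** It applies to any village, and control villages may leave too. Differential opt-out is plausible but is not stated.
- **That replacement by average villages produces a calculable bias.** If 3 of 35 IRS villages at 1.5 times the average rate are replaced by average villages, the arm mean falls from (32 + 4.5)/35 = 1.043 to 1.0. The mean of the remaining 32 is also 1.0, so the fall comes from losing the villages. Replacement adds nothing to it.
- **That the rule removes refusal of spraying from the effect.** Opting out of the study is different from declining spraying. Nothing says that a village which declines spraying leaves the cohort.
- **That no suitable village is left.** The article says "Two of the 5 districts in URR have 70 villages suitable for the trial" and plans 2 × 35 = 70 clusters. Clusters may combine small villages, however, and the count covers only two districts.
- **That a neighbour would breach the 2 km rule.** It might, but nothing waives that criterion for a replacement.

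**Conclusion.** The concern holds in a limited form. As worded, the rule permits a never-randomised village to join an open-label comparison after allocation is known: from the notice of spraying onwards in year 1, and throughout the window in year 2. This is a rule badly fixed in the text, and not merely detail left to another document. Its direction and size of effect cannot be derived, and it may never be used. The argument for changing it is that replacement gives up the protection of randomisation for very little. Not replacing two lost IRS clusters costs about 1 point of power, and not replacing two in each arm costs 2 to 3 points. Those figures rest on a 30% effect, k = 0.43, 74.4 child-years per cluster and an assumed two-sided 5% level. The point merits correction but does not by itself put the trial's conclusion in doubt.

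**What to change.** Reword the sentence under Safety considerations so that:

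1. Replacement is allowed only for a village that opts out before randomisation.
2. After randomisation no village is replaced in the primary comparison. Every randomised cluster stays in its allocated arm with all available data, including a village that declines spraying but remains in follow-up and the person-time already observed in a village that leaves.
3. Opt-outs are reported by arm, with their timing relative to disclosure of allocation.
4. Any replacement made later for operational reasons enters a sensitivity analysis only. The text allowing it must be reconciled with the 2 km separation in Study area and participant eligibility, and with the year 2 net distribution in Study procedures and evaluations, which as written does not provide for a newly added village.

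The cost is a change of wording and the small loss of power shown above.
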